**Rationale for Choice of Control Group**

To assess the effects of CM on an appropriate comparator, we consulted the National Institute of Health’s Pragmatic Model for Comparator Selection in Health-Related Behavioral Trials [46]. According to the model, the best comparator is one that suits the goals of the research trial. Given that (1) the CanCope modules have demonstrated promising results when trialed independently in pilot studies and (2) this is the first efficacy trial to assess the effectiveness of the CM program in its entirety, this trial remains within the preliminary phases of the research process. We defined the goal of this trial as establishing how well CM compares to information currently readily available to cancer survivors seeking support to improve their general well-being.

Currently, patients with cancer and cancer survivors have access to a host of resources that aim to promote general QoL, often with a focus on diet, physical exercise, relaxation, and sleep. These resources are often disseminated freely on the web by cancer-specific (eg, Cancer Council, National Breast Cancer Foundation, Prostate Cancer Foundation Australia) and noncancer-specific (eg, Mind UK, Beyond Blue, and Black Dog Institute) community and government organizations. Therefore, two possible comparator options were considered: (1) a wait-list control condition versus (2) a basic lifestyle and well-being intervention targeting diet, exercise, sleep, and relaxation using free and highly accessible web-based resources.

Both options were evaluated against 7 key characteristics identified in the National Institute of Health model [46], which are summarized in Table 2. On the basis of these considerations, a 4-module web-based well-being or lifestyle comparator was chosen (ie, CL). CL is expected to be widely accepted by participants in comparison to a wait-list control group, which may result in high attrition rates, especially given the number of between-module surveys. Furthermore, a basic well-being program is deemed relevant and highly feasible, as we can draw on information available on the web and preexisting sleep resources used in sleep trials by researchers at Monash University. Most importantly, an active comparator controls for nonspecific components of the intervention, such as contact with researchers and expectancy or placebo effects, allowing for greater stringency in measuring the outcomes of interest. The primary limitation of using CL as a comparator is that improvements in diet, physical exercise, relaxation, and sleep may lead to sizeable improvements in secondary outcomes (ie, anxiety and depressive symptoms and QoL). However, the primary outcome of interest is emotion regulation. Given that the CL intervention does not focus specifically on emotions, we expect that any significantly meaningful improvements in emotion regulation will be smaller than those observed in the CM group.

**Table 2 table2:** Comparison of potential comparator conditions.

Characteristic	Wait-list control (no intervention for 8 weeks).	CL^a^ (four modules: diet, exercise, relaxation, and sleep).
Acceptability	Moderate—participants will eventually be given the CM^b^ program, however, they may not be content with completing multiple study assessments during the 8-week waiting period.	High—participants will be provided with a program that targets health areas of interest. All participants will eventually receive the CM intervention material.
Feasibility	High—no intervention needs to be developed.	High—it is easy to access resources on the web to disseminate (from sites such as Cancer Council). Our research group has existing sleep hygiene information specifically designed for oncological populations.
Formidability	Low—no intervention means that outcomes should not change because of the comparator.	Moderate—improving diet, physical activity, relaxation, and sleep can have an impact on lowering depressive and anxiety symptoms and potentially emotion regulation.
Relevance	High—most cancer survivors do not receive a mental health intervention after finishing primary treatment.	High—basic well-being information regarding diet, physical exercise, relaxation, and sleep is commonly disseminated by hospitals and organizations, and is freely available on the web.
Stringency	Low—the absence of a comparator intervention would not control for other factors such as expectancy or placebo effects or contact with researchers.	High—controls for “nonspecific” intervention effects, such as expectancy and placebo effects and contact with researchers. The 4 comparator modules would align with the 4 CM modules, thus closely matching the treatment intervention’s timing of modules.
Uniformity	Low—participants would not receive the same information as the treatment group during the assessment period.	High—participants in the comparator group would receive a parallel 4-module program and concurrent assessment surveys.

^a^CL: CanCope Lifestyle.

^b^CM: CanCope Mind.

#### Control Group: CL

In parallel to the CM modules, the CL group receives four internet-delivered modules that focus on different lifestyle domains: (1) diet, (2) physical activity, (3) relaxation, and (4) sleep. Throughout each 2-week module, participants are sent 2 activity links via email, whereby they are asked to apply what they have learned from the module (eg, *describe how you applied the module material to your life*
*over the past week* and *describe how you plan to apply the module material to your life over the next week*). Participants may take 3 to 10 minutes to complete each reflective activity on the web. Although the CL participants are sent fewer application activities on the web than the CM participants, they are still encouraged to apply the module material to their daily lives over the 2-week module duration. The content included in CL is publicly available, except for sleep hygiene information, which was developed by the Monash University sleep research group. The content of each module is outlined in the subsequent sections.

#### CL Module 1: Eating Well After Treatment

Module 1 comprises 1 video and 3 readings. The video was developed by the organization *Mind* (a mental health charity in the United Kingdom established by the National Association for Mental Health) and outlines 8 tips to improve well-being through healthy diet habits (eg, eat regularly, eat healthy fats, keep hydrated, and eat a variety of healthy vegetables). All the 3 readings were developed by the Cancer Council. The readings promote eating a healthy diet rich in fruits, vegetables, and whole grains to maintain well-being and reduce cancer risk and provide healthy recipes. Participants are encouraged to apply the healthy eating habits across the 2-week module.

#### CL Module 2: Staying Active After Treatment

Module 2 comprises 1 video and 1 reading. The video was developed by the organization *Mind* and outlines tips to encourage physical activity (eg, starting small and adhering to a consistent routine). Participants are directed to the Cancer Council’s reading; “Exercise for people living with cancer,” which provides various exercises related to strength training, aerobic exercise, flexibility, and strengthening the pelvic floor. Participants are encouraged to choose 2 exercises listed in the reading (eg, strength training) to apply throughout the module.

#### CL Module 3: Relaxation for Mental Health

Module 3 comprises educational material (1 video and 1 reading) and a link to various guided relaxation audios. The 5-minute YouTube video was developed by the organization *Mind* and outlines 8 tips to aid relaxation (eg, scheduling regular breaks, diaphragmatic breathing, visualization techniques, and listening to music). The reading, titled “Learning to relax,” was developed by the Cancer Council and discusses healthy ways to manage emotional stress and aid relaxation (eg, exercising, massage, and yoga). Finally, participants are sent a link to access Beyond Blue’s guided relaxation audio clips. Participants could choose from (1) breathing exercises, (2) muscle relaxation, and (3) guided visualizations. Participants are encouraged to listen to any of these audio clips as many times as they would like across the 2-week module.

#### CL Module 4: Sleeping Well After Treatment

The final module comprises 2 readings focused on sleep and fatigue. The first reading was developed by the Cancer Council and explains fatigue in the context of cancer and ways to manage fatigue. The second reading provides education on sleep (eg, what is sleep, stages of sleep, and the importance of sleep) and various sleep hygiene tips (eg, reducing caffeine intake, reducing light exposure at night, and increasing light exposure in the morning). This informational sheet was developed by researchers at Monash University. Participants are encouraged to apply the sleep hygiene tips across the 2-week module.

### Assessment Time Points and Measures

Table 3 summarizes the nature and timing of the assessments in this trial. The research outcomes are assessed via web-based surveys administered via REDCap concurrently to both the CL and CM groups at the following time points: baseline (T_0_, approximately 25 minutes), after module 1 (T_1_, approximately 10 minutes), after module 2 (T_2_, approximately 10 minutes), after module 3 (T_3_, approximately 10 minutes), after module 4 (T_4_, after the intervention, approximately 25 minutes), and at the 3-month follow-up (T_5_, approximately 25 minutes). Participants in the CL are automatically emailed a link to complete each postmodule survey approximately 14 days after starting a given module. For CM participants, the postmodule surveys are automatically scheduled to be sent only once the core activities are completed (core activities are outlined in Table 1). Participants in both CL and CM are unable to begin the subsequent module until they have completed the previous postmodule survey. If participants do not complete their postmodule surveys within 2 weeks of receiving their original survey link, they are withdrawn from the study. Any completed survey responses beyond the 2-week cut-off time point are considered invalid and excluded from the analyses.

**Table 3 table3:** Schedule of survey assessments.

Time point				Items per time		Baseline (T_0_)^a^		Postallocation^a^								Follow-up (T_5_)^a^		
								T_1_ after module 1		T_2_ after module 2		T_3_ after module 3		T_4_ after module 4				

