### Secondary Aims

#### Aim 2 (Exploratory)

Aim 2 is to explore the role of each of the CM modules and whether the intervention is associated with changes in module-specific target outcomes (see Table 1 for CM modules and their associated outcomes).

**Table 1 table1:** CM^a^ module outline and outcomes.

Module	Description	Module-specific outcomes
1. Understanding emotions	Part 1 (2 days): learn about the adaptive functions of emotions. Day 1^b^ is a core activity. Part 2 (2 days): learn about unhelpful beliefs about emotions. Part 3 (10 days): learn about the 3-component model of emotional experiences (thoughts, feelings or physical sensations, and behaviors). Explore each component in one’s daily life. Day 5^b^ is a core activity.	Decrease unhelpful beliefs about emotions (BES^c^ [39])
2. Mindful emotion awareness	Part 1 (7 days): learn about mindfulness and nonjudgment of emotions. Practice mindfulness using daily 10-min guided audios. Day 1^b^ is a core activity. Part 2 (7 days): practice daily “anchoring” techniques to ground oneself in the present moment. Day 8^b^ is a core activity.	Increase mindfulness skills (SMQ^d^ [40])
3. Flexible thinking	Part 1 (14 days): learn about common “thinking traps” (ie, cognitive distortions such as catastrophizing) and how to challenge cognitive distortions. Practice daily cognitive reappraisal exercises to develop balanced thinking patterns. Day 1^b^ is a core activity.	Increase use of cognitive reappraisal strategies (CERQ^e^, UP-CSQ^f^ [32,41])
4. Doing things differently	Part 1 (6 days): learn about the impact of unhelpful EDBs^g^ (eg, avoidance) in perpetuating negative thoughts or emotions. Practice identifying one’s own EDBs. Day 1^b^ is a core activity. Part 2 (8 days): learn about the importance of challenging EDBs. Practice replacing unhelpful EDBs with healthier alternative actions (eg, approach-oriented rather than avoidance-oriented behaviors). Day 7^b^ is a core activity.	Decrease experiential avoidance (MEAQ-30^h^ [42])

^a^CM: CanCope Mind.

^b^Each module comprises 1 to 2 *core activities*, which must be completed for participants to finish the module and move on to the next module.

^c^BES: Beliefs About Emotions Scale.

^d^SMQ: Southampton Mindfulness Questionnaire.

^e^CERQ: Cognitive Emotional Regulation Questionnaire.

^f^UP-CSQ: Unified Protocol–Cognitive Skills Questionnaire.

^g^EDBs: emotion-driven behaviors.

^h^MEAQ-30: Multidimensional Experiential Avoidance Questionnaire-30.

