#### Primary Aim

Missing data are ubiquitous in research, and dropout and incomplete data (eg, dropout) are particularly common in web-only trials [62]. For aim 1 analyses, we will address missing data using multiple imputation with a fully conditional specification [63] and predictive mean matching [64]. A total of 20 imputed data sets will be generated. The primary outcome of the trial is the Difficulties in Emotion Regulation Scale (DERS-SF). The primary end point is immediately after the intervention, immediately following module 4 (T_4_). Anxiety and depression symptoms as well as overall QoL are secondary outcomes. All outcomes are continuous measures.

The primary analyses will consist of linear regressions on multiple imputed data. Each outcome variable at the primary end point (T_4_) will be included as the outcome variable in a linear regression, with group as the main predictor and the outcome variable at baseline (T_0_) and stratification factors included as covariates. Adjusted means in each group, as well as the adjusted mean difference, will be calculated. In the event of outliers, quantile regression will be used in place of linear regression and adjusted median differences at the primary end point (T_4_), and as exploratory analyses, the other time points will be estimated. Following recent research suggestions [65], we chose to provide randomization-based inferences; that is, statistical significance will be based on Fisher exact *P* values [66] from 100,000 permutations for the adjusted mean differences and uncertainty intervals will be based on 95% Fisher intervals. The sharp null hypothesis tested will be that being randomized to CM has an identical effect on participants’ outcomes as being randomized to CL.

Given the conceptual overlap between stratification factors and the outcome measured at baseline, only the stratification factors for anxiety and depression will be included in the linear regression assessment of the primary outcome (DERS-SF). For the linear regression assessment of depression and anxiety symptoms, only the DERS-SF stratification factor will be included. For the linear regression assessing QoL, both stratification factors will be included.

In addition to testing for group differences at the primary end point (T_4_), we will explore group differences at T_1_, T_2_, T_3_, and T_5_ on the primary and secondary outcomes. The overall sample mean at T_0_ will be presented for comparison.

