#### Sensitivity Analyses

Planned sensitivity analyses will include (1) calculating parametric and asymptotic *P* values and CIs, (2) generalized additive models to examine whether results differ when allowing nonlinear associations between baseline and postintervention symptoms, (3) per-protocol analyses based only on participants who completed all core intervention components, and (4) assessing group differences in intervention duration and the impact of intervention completion time on outcomes.

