### Limitations

The results of this trial will be interpreted in the context of its limitations. For instance, as the treatment group’s effects will not be compared against the absence of any intervention (eg, wait-list control), we will not be able to assess whether improvements in either group are due to the actual interventions or a result of naturalistic tendencies (eg, natural improvement in mental health symptoms over time). In addition, the intervention intensity and thus the potential duration of CM and CL differ. Unlike in CL, CM includes mandatory core activities in each module, which must be completed before participants can progress to the subsequent modules. This means that CM participants are likely to take longer to complete the intervention, which could impact the outcomes and attrition rates. Finally, CM and CL are English language–based interventions, and the trial excludes those who cannot read or write in English, which may limit the generalizability of findings to English-speaking populations only.

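### The T4 survey is released on treatment activity in CM but not in CL, so every observed CM primary outcome comes from a core completer, and no listed analysis tests the imputation that fills the rest

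*Protocol article*

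**What the plan says.** All of this is in the protocol article.

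- **Survey release** (Assessment Time Points and Measures). For CM: "For CM participants, the postmodule surveys are automatically scheduled to be sent only once the core activities are completed". For CL: "Participants in the CL are automatically emailed a link to complete each postmodule survey approximately 14 days after starting a given module". The same section describes the surveys as given to both groups at the same time.
- **Gates common to both arms** (same section). "Participants in both CL and CM are unable to begin the subsequent module until they have completed the previous postmodule survey". Also: "If participants do not complete their postmodule surveys within 2 weeks of receiving their original survey link, they are withdrawn from the study". Later responses are excluded.
- **Core activities** (Table 1 and its footnote). "Each module comprises 1 to 2 *core activities*, which must be completed for participants to finish the module and move on to the next module". The table marks seven of them.
- **Analysis basis** (Data Cleaning and Sample Characteristics). Intention-to-treat.
- **Missing data** (Primary Aim, within the Statistical Analysis Plan). "we will address missing data using multiple imputation with a fully conditional specification", with predictive mean matching and 20 imputed data sets.
- **Sensitivity analyses.** Four are listed: parametric and asymptotic inference; generalized additive models; "per-protocol analyses based only on participants who completed all core intervention components"; and intervention duration with its effect on outcomes.
- **Acknowledged limitation** (Limitations). "Unlike in CL, CM includes mandatory core activities in each module, which must be completed before participants can progress to the subsequent modules". The authors expect CM probably to take longer and accept that outcomes and attrition could be affected. They do not discuss what this does to the intention-to-treat label.

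**The concern.** Whether the primary outcome is collected depends on treatment activity in one arm only. A CM participant who stops before finishing the core activities of a module is not sent that module's survey, cannot start the next module, and so never receives T4. The article describes no other route to a T4 score. A CL participant who ignores the content but answers the surveys does supply T4.

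Every observed CM score at the primary end point therefore comes from someone who completed all core activities. An intention-to-treat effect also needs the outcomes of those who stopped, and the design does not collect them. Standard imputation has to assume that stoppers, given their observed data, would have scored like completers of their own arm. If they benefit less, the primary estimate is too favourable to CM.

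The listed sensitivity analyses would not reveal this. Parametric inference and additive models keep the same missing-data assumption. In CM the per-protocol set is essentially the participants who already have T4. The duration analysis addresses timing, not outcomes that were never collected.

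**Working it through.** **Inputs from the article.** Randomized: CM 110, CL 114 (of 224: 49.1% and 50.9%, as stated). T4 completed: CM 61, CL 75 (Results). SMD 0.5 and baseline-to-T4 correlations of 0.3 to 0.6 (Power Analysis), used here only as a scale. The article gives no figure for the bias itself, so there is none to reproduce.

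**1. What the CM gate requires.** Core activities by module: 2 + 2 + 1 + 2 = 7, out of 4 × 14 = 56 daily activities.

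**2. Missing T4.**
- CM: 110 − 61 = 49; 49/110 = 44.5%.
- CL: 114 − 75 = 39; 39/114 = 34.2%.
- Difference 10.3 percentage points (chi-square p = 0.11, Fisher p = 0.13). The point does not rest on this difference.

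**3. Intention-to-treat effect implied by a completer effect.** Let p = 61/110 = 0.555, and let f be the share of the completer effect kept by CM stoppers. The article gives no value for f, so it is varied.

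ITT effect = 0.50 × [p + (1 − p) × f]

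| f | ITT effect (SD) |
|---|---|
| 0 | 0.50 × 0.555 = 0.28 |
| 0.25 | 0.50 × (0.555 + 0.111) = 0.33 |
| 0.5 | 0.50 × (0.555 + 0.223) = 0.39 |
| 1 | 0.50 |

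**4. What imputation returns.** Trials were simulated with the article's arm sizes and completion counts. Predictive mean matching used group as a predictor and donors pooled across arms. Assumptions: correlation of 0.5 between waves, dropout unrelated to outcome, 5 imputations, 600 trials per setting.

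| f | ITT, full data | Completers only | Imputed, with T1–T3 |
|---|---|---|---|
| 0 | 0.27 | 0.50 | 0.49 |
| 0.5 | 0.38 | 0.50 | 0.49 |
| 1 | about 0.50 | about 0.50 | about 0.49–0.50 |

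If stoppers' interim scores already show the reduced benefit, imputation using T0 to T3 recovers part of it. The estimate is then about 0.42 to 0.45 against a true 0.28 (f = 0), and about 0.45 to 0.47 against 0.38 to 0.40 (f = 0.5). These figures depend on how early the loss of benefit shows in the interim scores.

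**5. How fragile an estimate of 0.50 would be.** Worsening every imputed CM value by δ SD lowers the estimate by 0.445 × δ. Taking SE = √(1 − r²) × √(1/61 + 1/75) and holding it fixed:
- r = 0.3: SE = 0.954 × 0.172 = 0.164; δ = (0.50 − 1.96 × 0.164)/0.445 = 0.40.
- r = 0.6: SE = 0.800 × 0.172 = 0.138; δ = (0.50 − 1.96 × 0.138)/0.445 = 0.52.

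A shift of about 0.4 to 0.5 SD, comparable with the whole assumed effect, would remove significance.

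**The case against.** Several objections narrow the point, and most of them stand.

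- **CL is selected too.** A reader might infer that adherent CM is compared with an unselected CL. It is not: CL also needs timely T1 to T3 surveys, and 39 of 114 lack T4. What remains is the additional activity condition in CM.
- **The gate is light.** It covers 7 of 56 activities, none later than day 8 of a module. Observed CM participants are core completers, not highly adherent users.
- **Timing.** A reader might infer that CM's T4 is later by design. The article says only that CM is likely to take longer, both programs can finish in as few as 8 weeks, and the fourth sensitivity analysis examines duration.
- **T5.** The gate is stated for postmodule surveys. The article does not say whether CM stoppers receive the 3-month follow-up, so it cannot be said that no outcome is ever seen after stopping.
- **Imputation detail.** Predictors are not listed, the phrase missing at random is not used, and the sensitivity list is not worded as exhaustive. A fuller analysis plan may say more.
- **Per-protocol set.** The article refers to core components rather than core activities and does not define them for CL. The overlap with T4 completers is a close inference for CM only.

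The last two points do not remove the concern. It rests on a stated collection rule rather than on missing detail, and standard imputation by this method carries the missing-at-random assumption.

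**Conclusion.** The point holds in a limited form. It is certain that the stated rule leaves no T4 score for CM participants who stop the core activities, and that 44.5% of CM primary outcomes would be imputed from core completers under an intention-to-treat label. The direction, overstatement of CM, holds if stoppers benefit less. The size is not known.

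An overstatement of 80% (0.50 against 0.28) is tempting to quote, but it is a worst case: a 0.50 SD completer effect, stoppers keeping nothing even after finishing some modules, and interim scores that carry no information. With informative T1 to T3 scores the excess is smaller (about 0.42 to 0.45 against 0.28), and it is nil if stoppers keep the full effect. Nor do the documents support reading this as an invalid test of the sharp null: under this dilution mechanism, a zero effect in completers gives zero bias.

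**What to change.** 1. **State the estimand**, including how outcomes after stopping the core activities are treated.
2. **Include T1 to T3 scores in the imputation model.**
3. **Add a delta-adjusted tipping-point analysis** for the missing CM T4 values as a key sensitivity analysis, reported beside the primary result. Reference-based imputation from CL can be added. It assigns active-control outcomes to people who never received CL, so it should be optional and labelled as such.
4. **Do not present the per-protocol analysis as a check on missing data.**
5. **Reconcile the statement that both groups are surveyed at the same time** with the two different triggers.

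Releasing surveys on one schedule in both arms, whether or not core activities are done, is the design remedy, and module gating could stay. Follow-up data collection ended in April 2022, so that applies only to future use of the design. A complier-average effect is no substitute, because it needs the T4 outcomes of CM non-compliers that were not collected.

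The cost is plan wording and some computation. The drawback is that the sensitivity estimate may be smaller than the primary one.
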